## Abstract

**Background:**

Plaque psoriasis is a refractory inflammatory skin disease. The common therapies used to treat plaque psoriasis in traditional Chinese medicine (TCM) and western medicine (WM) have distinct characteristics and advantages. Although a combination of TCM and WM therapies, adjusted to the clinical situation, is widely used, there are no systematic studies on the hierarchical selection of this treatment combination based on the severity of skin lesions. We therefore designed a randomized clinical trial to focus on the sequence of internal and external treatments of TCM in patients with mild-to-moderate plaque psoriasis and to optimize the integration of Chinese and western medicine for the treatment of patients with severe plaque psoriasis, thereby achieving high-level clinical evidence and establish treatment norms for the integrated use of Chinese and western medicines.

**Methods:**

In this proposed multicenter, single-blinded, randomized controlled trial, 108 patients with mild-to-moderate plaque psoriasis will be randomly assigned to two groups in a 1:1 ratio to receive either internal or external TCM treatment, and 270 patients with severe plaque psoriasis will be randomly assigned to three groups in a 1:1:1 ratio to receive treatment with TCM or WM, or TCM + WM. All enrolled patients will receive 8 weeks of treatment. Follow-up assessments will be done 8 weeks after the treatment. The primary outcome of this study is the evaluation of efficacy and relapse rate, based on the Psoriasis Area and Severity Index, and the secondary outcome measures include determination of the affected body surface area, physician’s global assessment, pruritus scores (determined using a visual analog scale), TCM symptom score, Dermatology Life Quality Index, patient-reported quality of life score and incidence of serious adverse events.

**Discussion:**

This study will provide high-level clinical evidence for internal and external TCM treatment optimization and will contribute to establishing norms for the integration of Chinese and western Medicines.

**Trial registration:**

ClinicalTrials.gov, NCT03941431. Registered on 8 May 2019.

## Introduction

### Background and rationale

Psoriasis is a common chronic relapsing inflammatory skin disease with a prevalence rate of 2–4% [1]. Although its underlying cause is not fully understood, it is generally associated with genetic, metabolic, immunological, endocrinal and infective etiologies [2]. Psoriasis, particularly refractory plaque psoriasis, can have considerable detrimental effects on the patient’s quality of life. In western medicine (WM), treatments for psoriasis, such as topical corticosteroids, vitamin D derivatives, calcineurin inhibitors, systemic phototherapy, acitretin, cyclosporine A, immunosuppressants and biological agents [3], can alleviate the clinical symptoms to varying degrees. However, the potential safety problems and high costs associated with the use of these agents often limit their clinical application.

The treatment of psoriasis using traditional Chinese medicine (TCM) has a long history, with the earliest records traced back to more than 1400 years ago. It is based on a completely theoretical system, which has evolved progressively in response to technological developments and lifestyle changes. A series of systematic reviews of TCM in clinical practice have indicated that this approach is effective in the treatment of psoriasis [4–10], and clinical and experimental data indicate that TCM can modify psoriasis by antagonizing or regulating interleukin (IL) and the IL-23/IL-17 axis to inhibit the main causal pathways [11].

In a clinical trial conducted by our research team, we found that treatment with Jueyin (JY, 决银, 決銀) prescription, a compound Chinese herbal preparation containing seven constituents (abalone shell, honeysuckle, tree peony bark, dried rehmannia root, *Hedyotis diffusa*, folium and turmeric root tuber; Table 1) is safe and effective in patients with early-stage psoriasis [12]. Its mechanism of action is related to the inhibition of keratinocyte proliferation, enhancement of epidermal parakeratosis, and reduction in nitric oxide and malondialdehyde [13]. These assumptions have accordingly been verified in in vitro studies, in which a 5% JY prescription had a significant inhibitory effect on the proliferation of HaCaT cells, with primary effects on the G1 phase of the cell cycle [14].

**Table 1 Tab1:** Constituents of the Jueyin prescription

Main constituents	Scientific name	Plant part(s)
Abalone shell	*Concha haliotidis*	Shell
Honeysuckle	*Lonicera japonica* Thunb	Flower
Tree peony bark	*Cortex Moutan*	Bark
Dried rehmannia root	*Rehmannia glutinosa* Libosch	Root
Hedyotis diffusa	*Hedyotis diffusa* Willd	Whole grass
Folium	*Isatidis*	Leaf
Turmeric root tuber	*Curcuma aromatica* Salisb	Root

In TCM, the moving cupping therapy is a type of acupuncture therapy, commonly used in China and other Asian countries, and is gradually gaining worldwide acceptance owing to its simplicity, convenience and effectiveness [15]. Compared to treatment with oral Chinese medicine alone, a more pronounced decrease in Psoriasis Area and Severity Index (PASI) score has been recorded in psoriasis patients treated with moving cupping therapy combined with TCM [16]. In this procedure, a vacuum is generated by heating air in a cup with a flame and placing the cup over skin lesions. The cupping produces a mild attraction in the skin, which is characterized by a strong adsorptive force and a deep action on skin lesions. Coupled with the rapid push and pull of the cup against the body at the site of the skin damage, cupping accelerates blood circulation and promotes metabolism, dissipates blood stasis, regulates meridians and collaterals, and stimulates the overall vitality of the body to strengthen its resistance and eliminate pathogenic factors. Previous studies have shown that the moving cupping therapy combined with TCM ointment is effective in the treatment of plaque psoriasis, having an effect equivalent to the exposure to narrow-band ultraviolet B radiation (NB-UVB) combined with externally applied calcipotriol ointment [17].

NB-UVB phototherapy is a common and effective method for the treatment of plaque psoriasis. An optimal wavelength of 313 nm of NB-UVB phototherapy has been shown to have high efficacy and a small side-effect profile [18, 19]. It has been reported that UV light affects various components of the natural and acquired immune responses and is related to the depletion of both the Langerhans cells and T cells in the epidermis [20–22]. Previous studies have indicated that, in patients with psoriasis, the serum levels of 25-hydroxyvitamin D increase in response to NB-UVB treatment, and there is a correlation between this increase and the number of therapy sessions [23]. Moreover, changes in the skin microflora following UVB treatment may be related to treatment response [24]. These findings thus indicate that the effectiveness and safety of phototherapy on psoriasis may depend on a complex interaction of immunological and metabolic mechanisms. In addition, according to clinical reports, NB-UVB combined with a TCM-medicated bath can improve the curative effect, reduce the cumulative dose, and lessen the adverse reactions of UV radiation compared to exposure to NB-UVB alone [25].

### Objectives

Although TCM and WM are both commonly used in the treatment of psoriasis and each has its own associated advantages and characteristics, the combined application of these two approaches can enhance the curative effect and reduce the side effects and recurrence rate of psoriasis. Therefore, the combination of TCM and WM therapies, adjusted according to the clinical situation, has been used widely in medical practice. However, there have been no previous clinical studies examining the hierarchical selection of treatment combinations according to the severity of skin lesions. To date, only the pairwise combinations of Chinese herbal medicine, cupping therapy and NB-UVB phototherapy for plaque psoriasis have been reported, and the curative effects were found to vary. Therefore, in this multicenter, randomized controlled, single-blind clinical trial, “Our Choice”, we combined JY granules (JYG) and moving cupping therapy for the treatment of mild-to-moderate plaque psoriasis, while for severe psoriasis we combined JYG, moving cupping therapy and NB-UVB phototherapy. This study aimed to optimize the internal and external TCM treatments and establish a high level of clinical evidence and treatment norms for the integration of Chinese and western medicines.

### Trial design

This is a multicenter, single-blinded, randomized controlled trial that aims to determine the appropriate time for the intervention with TCM and involves a sequential treatment plan for severe psoriasis by combining TCM and WM.

The study consists of three phases: screening, treatment and follow-up. During the initial screening period, patients will be recruited to dermatological clinics for body surface area (BSA) assessments and laboratory tests (including pregnancy tests for women of child-bearing age), and they will also be assessed on the designated inclusion and exclusion criteria. The eligible patients will be required to sign a written informed consent form, including an option to participate in the biobank initiative. The investigator will clearly explain to the patients all the details in the consent form, ensuring that they are fully aware of their rights and are able to cooperate with the researchers to complete both the treatment and follow-up phases. Patients who provide their informed consent and meet the laboratory test criteria will undergo the medical procedures, based on their BSA score. According to the latest Chinese guidelines for severity, psoriasis is classified into the following categories: mild (lesion area <3% BSA), moderate (lesion area 3–10% BSA) and severe (lesion area >10% BSA) [26]. In this study, only those patients with skin lesions involving 10–15% BSA will be included in the severe group.

Patients with mild-to-moderate plaque psoriasis will be randomly assigned to one of two groups in a 1:1 ratio, where one group will receive JYG and moving cupping placebo therapy and the other group will receive JYG placebo (JYGP) and moving cupping therapy. The patients in these two groups will be evaluated after 4 weeks of treatment. If a 75% reduction in the PASI (PASI 75) is achieved, treatment will be continued until the end of the 8-week study. Otherwise, patients receiving the moving cupping placebo therapy will be switched to moving cupping therapy, and those receiving JYGP will be switched to JYG for the subsequent 4 weeks of treatment. Patients with severe plaque psoriasis will be randomly assigned to one of three groups in a 1:1:1 ratio to receive JYG, moving cupping therapy and NB-UVB placebo therapy, or JYGP, moving cupping placebo therapy and NB-UVB therapy, or JYG, moving cupping therapy and NB-UVB therapy (Fig. 1). At each visit, we will evaluate and record the relevant patient efficacy indicators and TCM symptom information and obtain images of target lesions. This manuscript has been written in accordance with the Standard Protocol Items: Recommendations for Interventional Trials (SPIRIT) 2013 checklist (see Additional file 1). The results of the study will be disseminated to the public through conference reports and open-access journals.

**Fig. 1 Fig1:**
[figure not shown]
Study flowchart. BSA body surface area, NB-UVB narrow-band ultraviolet B radiation, PASI 75 75% reduction in the Psoriasis Area and Severity Index, TCM traditional Chinese medicine, WM western medicine

## Methods: participants, interventions and outcomes

### Study setting

The study will be conducted at the following six centers in China: the Shanghai Yueyang Integrated Medicine Hospital, the Shanghai Dermatology Hospital, the Chinese Medicine Hospital Affiliated to the Southwest Medical University, the Wuhan No. 1 Hospital, the Second Affiliated Hospital of Fujian Traditional Chinese Medical University and the Affiliated Hospital of the Nanjing University of Chinese Medicine. Patients will be assessed in the dermatology departments of each hospital. Each study center has a solid work foundation and sufficient outpatient volume, which provides supporting conditions for the completion of this study.

### Eligibility criteria

#### Inclusion criteria

To be eligible for recruitment, the patient must:
Have plaque psoriasis; the course of the disease is not limitedHave skin lesions covering ≤15% of the BSA (it should be mainly located on the trunk and/or limbs, palms/soles and face/scalp; the vulva area should not be included)Aged between 18 and 65 yearsProvide informed consent

#### Exclusion criteria

Patients who meet any of the following criteria will not be eligible for recruitment:
Patients with other active skin diseases that may affect condition assessmentPatients who have received systematic treatment with research drugs, biological agents or immunosuppressive agents within 2 months prior to screeningPatients who have received treatment with topical glucocorticoids, retinoic acid or phototherapy within 2 weeks prior to screeningPatients with severe, uncontrollable local or systemic acute or chronic infectionsPatients with severe systemic diseases or any of the following clinical test indicators: an increase in alanine transferase or glutamate transferase level >1.5 times the upper limit of normal or an increase in serum creatinine level >1.5 times the upper limit of normal; patients with any of the main standard blood indicators (i.e., white blood cell count, red blood cell count, hemoglobin level and platelet count) below the lower limit of normal, or those with other laboratory abnormalities as judged by the investigators, will be excludedPatients with a history of malignant tumors or primary/secondary immunodeficiency and hypersensitivityPatients who have undergone a major surgery within 8 weeks of treatment or will require such surgery during the study periodPatients who are pregnant or lactatingPatients with a history of alcohol or drug abusePatients with a history or family history of a serious mental illnessPatients with a family history of cancerPatients who were judged by the investigators to be unsuitable for inclusion in the study for any other reasons

### Who will take informed consent?

All patients will receive professional and practical knowledge of their daily treatment and nursing from a team of researchers, including senior experts in the field of TCM for psoriasis and will be provided with feedback on the results of the relevant assessment on completion of the study. When signing the informed consent form, the patients will be informed of the burden of the study and their freedom to withdraw from the study at any time. In case patients decide to withdraw from the study, they will be required to undergo a final evaluation of efficacy and safety.

### Interventions

#### Intervention description

Patients in the TCM internal treatment group (group A) will receive JYG twice daily after meals and moving cupping placebo therapy three times weekly for 8 weeks, while patients in the TCM external treatment group (group B) will receive JYGP twice daily after meals and moving cupping therapy three times weekly for 8 weeks. Patients in the TCM treatment group (group C) will receive JYG twice daily after meals and moving cupping therapy and NB-UVB placebo therapy three times weekly for 8 weeks, while those in the WM treatment group (group D) will receive JYGP twice daily after meals and moving cupping placebo therapy and NB-UVB therapy three times weekly for 8 weeks. In the TCM + WM treatment group (group E), the patients will receive JYG twice daily after meals and moving cupping therapy and NB-UVB therapy three times weekly for 8 weeks.

#### Moving cupping therapy

According to the body position requirements during the moving cupping therapy, the patient will be asked to take a suitable sitting or lying position. Subsequently, the operator will expose the local skin, select the acupoint location, and apply a small amount of Vaseline oil to lubricate the skin after routine disinfection. Cups of appropriate size with smooth mouths will be used. The operation will start after disinfection. The operator will adhere to the following procedure during the operation: using the left hand to hold a 95% alcohol cotton ball, the operator will ignite the middle and lower sections of the cup. The operator will then take the cup out after moving it in a circle. Next, holding the cup in his right hand, he will quickly place it at the concentrated site of the lesion, pushing it toward the distal end and turning back. These steps will be repeated several times. Patients will be required to wear an eye patch during the entire operation. Slow walking refers to moving the cupping back and forth approximately once per second, whereas fast walking refers to moving the cupping back and forth approximately twice per second. According to the clinical requirements, a combination of light adsorption and slow walking, light adsorption and fast walking, heavy adsorption and slow walking, and heavy adsorption and fast walking should be chosen. The combination of heavy adsorption and fast walking is often used in the lower back or limbs of patients with plaque psoriasis. The cup will be replaced every five times, with an interval of no more than 10 s. Each part of the moving cupping will be positioned on the patient’s skin about 30 times until the local skin appears reddish, red, crimson or purplish.

#### Moving cupping placebo therapy

The procedure for moving cupping placebo therapy will be similar to the moving cupping therapy. In this operation, the same glass cup will be used except that it will have 6 mm holes drilled in the top. Patients undergoing the moving cupping placebo operation will also need to wear an eye patch during the procedure. After the oxygen combustion in the cup is consumed, the air can enter through the small hole to supplement it; therefore, the negative pressure adsorption force will not be formed. This simulates moving cupping therapy without the therapeutic effect and is similar to mild scraping therapy, leaving a similar reddish mark on the skin (Fig. 2).

**Fig. 2 Fig2:**
[figure not shown]
Cups used in the moving cupping therapy and placebo therapy. **a** Cups used in the moving cupping therapy. **b** Cups used for moving cupping placebo therapy

#### Strategies to improve adherence to interventions

All patients in each of the treatment groups will be provided with a free of charge emollient (YuZe Skin Barrier Recovery Body Lotion®; developed by the Rui Jin Hospital and produced by Shanghai Jahwa United Company, China) as basic skin care. We anticipate that this will enhance patient compliance. To document compliance, patients will be required to record the dose of the oral granules and the time of administration in a daily diary of medication. At each visit, the researchers will record the application dates and doses of emollients, drugs, moving cupping therapy and NB-UVB phototherapy. Unused emollients and drugs will be returned to the hospital prior to the distribution of new emollients and drugs.

In the preparatory phase of the trial we fully considered the time cost of each follow-up. In the debugging phase of the case management system we added the mobile telephone upload function of the patient laboratory examination report and skin lesion photos and set up the treatment follow-up reminder function to reduce the loss of visit rate. The patients who do not follow-up on time will receive repeated reminders from researchers in the time window.

### Outcomes

#### Primary outcome

The primary outcome in this trial is evaluation of the efficacy and incidence of relapse in response to sequential treatment with integrated Chinese and western medicines during the treatment and follow-up periods. Relapse is defined as a PASI score exceeding the baseline score at the time of enrollment or development of new pustules or erythroderma [27]. PASI will be assessed at baseline, at 2-week intervals during the treatment period, and at 4-week intervals throughout the follow-up period.

#### Secondary outcomes

The secondary outcome measures in the study are: 1) improvement in BSA; 2) improvement in physician’s global assessment (PGA); 3) visual analog scale (VAS) scores for pruritus; 4) improvement in TCM symptom score; 5) improvement in the Dermatology Life Quality Index (DLQI) and patient-reported quality of life (PRQoL); and 6) incidence of serious adverse events (SAEs).

The BSA, PGA, VAS score, TCM symptom score, DLQI and PRQoL will be assessed at baseline, at 2-week intervals during the treatment period, and at the end of the follow-up period. Laboratory tests, including complete blood counts, urinalysis, and hepatic and renal function tests, will be performed at baseline and at 8 weeks after treatment (Table 2).

**Table 2 Tab2:**
[figure not shown]
Schedule for treatment and outcome measurements

*BSA* body surface area, *DLQI* Dermatology Life Quality Index, *JYG* Jueyin granules, *JYGP* Jueyin granules placebo, *NB-UVB* narrow-band ultraviolet B radiation, *PASI* Psoriasis Area and Severity Index, *PASI 75* 75% reduction in the Psoriasis Area and Severity Index, *PGA* Physician Global Assessment, *PRQoL* patient-reported quality of life, *VAS* visual analog scale, *TCM* traditional Chinese medicine

### Sample size

The sample size for this study was calculated based on the expected value of the efficacy based on the results from previous studies [17, 28]. The efficacy rates for groups A, B, C, D and E were 30.0%, 59.0%, 73.0%, 55% and 88.0%, respectively. The significance level (alpha) was set at 0.05 and the statistical power was 80%. Based on our calculation using the PASW statistical software (V.18.0), a sample size of 43 patients was required for groups A and B and 72 patients for groups C, D and E. However, considering a potential 25% loss of patients during follow-up, we adjusted the total sample sizes of groups A and B to 54 patients and that of groups C, D and E to 90 patients.

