### Statistical methods

All analyses will be performed by applying the SPSS V.21.0, (SPSS Inc., Chicago, IL, USA) statistical software and the data network platform designed by the data management center of Jiangsu Famaisheng Medical Technology. The outcome investigators will be blinded to group allocation. According to the principle of an intention-to-treat analysis, all patients who will be randomized and evaluated according to the efficacy indicators at least once are defined as the full analysis set population, whereas all patients who meet all inclusion and exclusion criteria and deviated from the prescribed dose less than 20% of the regimen are defined as the per-protocol set population. Patients who received treatment one or more times and have at least one safety evaluation will be analyzed in the safety set population. The efficacy measurement will be evaluated mainly by intention-to-treat analysis (full analysis set) and supplemented by per-protocol analysis. The safety evaluation will be analyzed in the safety set population.

If a numerical variable shows normal distribution and the variance is uniform, the statistical description will be expressed as the mean ± standard deviation; the statistical inference will be expressed by the F and S-N-K tests; and the repeated measurement of data analysis of variance will be used for comparison among the groups at multiple time points. In case a numerical variable shows skewed distribution, the median and minimum and maximum values will be used for statistical description; the rank sum test and Nemenyi test will be used for statistical inference, and the generalized estimation equation will be used for comparison among the groups at multiple time points. For categorical variables, the frequency, constituent ratio and rate will be used for statistical description. If the analysis index is unordered, a chi-squared test will be used for statistical inference and, if the analysis index is ordinal, a nonparametric test will be used for statistical inference. The generalized estimation equation will be used for comparison among the groups at multiple time points. Hypothesis testing will be performed using a two-sided test with 95% confidence intervals. A *P* value less than 0.05 indicates statistical significance.

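### The 80% power stated for groups C, D and E matches no pairwise contrast at the protocol's own rates, and the 88% assumed for group E is an unlabelled extrapolation to which the E v C power is very sensitive

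*Protocol article*

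**What the plan says.** In the protocol article, Sample size, the size was "calculated based on the expected value of the efficacy based on the results from previous studies [17, 28"]. The inputs follow in one list: "The efficacy rates for groups A, B, C, D and E were 30.0%, 59.0%, 73.0%, 55% and 88.0%, respectively". The error rates are given once for all five groups: "The significance level (alpha) was set at 0.05 and the statistical power was 80"%. The result is "a sample size of 43 patients was required for groups A and B and 72 patients for groups C, D and E". After an allowance for loss, C, D and E become 90 each, and the abstract gives the same total: "270 patients with severe plaque psoriasis will be randomly assigned to three groups in a 1:1:1 ratio". The section does not say which comparison among C, D and E the 80% belongs to.

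Statistical methods fixes the sidedness: "Hypothesis testing will be performed using a two-sided test with 95% confidence intervals".

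Intervention description defines the three severe-disease groups: C is Jueyin granules plus moving cupping with placebo NB-UVB; D is NB-UVB with placebo granules and placebo cupping; E is all three active treatments.

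On the evidence for such combinations, the Objectives state: "To date, only the pairwise combinations of Chinese herbal medicine, cupping therapy and NB-UVB phototherapy for plaque psoriasis have been reported". They add that the effects varied.

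**The concern.** Two things in the Sample size section do not fit.

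The first is the power. Three groups with rates of 73%, 55% and 88% give pairwise differences of 18, 15 and 33 percentage points. One group size cannot give the same power for all three, so a single 80% must refer to one contrast or to an overall test, and the section does not say which. If it describes none of them, a reader will take E v C and C v D to be better powered than they are.

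The second is the source of the 88%. Group E is the triple combination, which by the protocol's own account had not been reported. Yet its rate stands beside the others, under the same attribution to previous studies, with nothing to mark it as extrapolated. Two of the three contrasts depend on it.

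At stake is how the severe-disease results are read. The trial is meant to support treatment norms for integrated care. If E v C is not significant, a reader who trusts the 80% may conclude that phototherapy adds nothing to the Chinese-medicine regimen, when the trial had a substantial chance of missing the difference that it assumed.

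**Working it through.** **Inputs.** From Sample size: A = 0.30, B = 0.59, C = 0.73, D = 0.55, E = 0.88; alpha 0.05; power 80%; 72 per group, then 90. From Statistical methods: two-sided tests, and a chi-squared test for unordered categorical outcomes. The loss allowance was applied as 72 × 1.25 = 90.

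**Step 1: the plan's own figures.** For A v B, with the unpooled formula n = (1.960 + 0.842)² × [p₁(1 − p₁) + p₂(1 − p₂)] / (p₁ − p₂)²:

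7.849 × (0.2100 + 0.2419) / 0.29² = 42.2, so 43. This agrees with the protocol. The pooled formula gives 45.

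For C, D and E, with the pooled formula n = {1.960 √[2p̄(1 − p̄)] + 0.842 √[p₁(1 − p₁) + p₂(1 − p₂)]}² / (p₁ − p₂)²:

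- E v C: (1.098 + 0.463)² / 0.15² = 108.3, so 109
- C v D: (1.330 + 0.561)² / 0.18² = 110.4, so 111
- E v D: (1.251 + 0.500)² / 0.33² = 28.2, so 29

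The unpooled formula gives 106, 108 and 26. An overall three-group chi-squared test needs about 36 per group. One-sided tests, a continuity correction, the arcsine formula and adjusted alphas of 0.025 and 0.0167 were also tried. None gave 72.

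**Step 2: power at the protocol's rates.** Exact power is the sum, over all pairs of responder counts (x, y), of Bin(x; n, p₁) × Bin(y; n, p₂) wherever the pooled chi-squared test without continuity correction is significant at two-sided 0.05.

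| Contrast | Rates | 72 per group | 90 per group |
|---|---|---|---|
| E v C | 88% v 73% | 64% | 73% |
| C v D | 73% v 55% | 61% | 72% |
| E v D | 88% v 55% | 99.6% | 99.9% |

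The normal approximation agrees closely: 62%, 62% and 99.5% at 72. The overall three-group test has about 98% power at 72. None of these is 80%.

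**Step 3: sensitivity to the group E rate.** C and D are held at the printed rates. Every E value below 88% is an assumption made to show the range.

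| E | E v C, n = 72 | E v C, n = 90 | E v D, n = 72 | E v D, n = 90 |
|---|---|---|---|---|
| 88% | 64% | 73% | 99.6% | 99.9% |
| 85% | 43% | 51% | 98% | 99.5% |
| 80% | 17% | 20% | 90% | 95% |
| 75% | 6% | 6% | 71% | 81% |

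At 72 per group, E v D crosses 80% at about E = 77%. E v C reaches 80% only at about E = 91%, above the protocol's own assumption.

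**Step 4: the source of the 88%.** The attribution to previous studies covers all five rates. The Objectives exclude an earlier report of the three treatments together. The Introduction describes reference 17 as cupping with a Chinese-medicine ointment, equivalent in effect to NB-UVB with calcipotriol, which is not group E's regimen. The text does not describe reference 28, but the statement in the Objectives covers it too. So 88% can only be extrapolated from other regimens.

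**The case against.** The strongest reply on the 88% is that the section speaks of an expected value. An expectation for a new combination, built from results on its parts, fits that wording, and the past tense may simply describe the inputs used. This stands: extrapolating is legitimate, and relabelling the rate would change no result by itself. What remains is that the reader cannot tell E's rate from those that may have been observed.

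On power, the protocol designates neither E v C nor E v D as the powered comparison, and the overall three-group test has about 98% power at 72 and stays above 80% down to about E = 78%. This also stands. The documents do not support saying that the severe-disease cohort is underpowered as a whole. They do support saying that 80% is not the power of any pairwise comparison.

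The number analysed could also lie anywhere between 72 and 90, because the full analysis set keeps anyone evaluated at least once. Both ends are therefore shown, and E v C and C v D are below 80% at both.

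An article may leave a derivation or a full sensitivity table to the full protocol. That is accepted. The point rests on a stated figure that does not follow from the stated inputs.

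Two stronger readings are tempting and should not be made:

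- **That the power shortfall comes from the doubtful source of the 88%.** It does not. E v C is already at 64% with 88% accepted in full, and C v D, which does not involve E, is at 61%.
- **That 88% was obtained by assuming that the effects of C and D act independently.** The product rule does give 1 − 0.27 × 0.45 = 0.8785, but nothing in the document mentions such a calculation, and one numerical match is not evidence of it.

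**Conclusion.** The point holds in this form. At the protocol's own rates, 72 per group does not give 80% power for any pairwise contrast: E v C and C v D fall 16 to 19 percentage points short, and E v D is far above. Analysing all 90 narrows the shortfall to 7 to 8 points but does not remove it.

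Separately, the 88% for group E is an extrapolation presented without a label. The practical consequence falls on E v C, where a drop of 3 points in the assumed rate, from 88% to 85%, lowers power from 64% to 43% at 72 per group. E v D is robust down to about E = 77% at 72 per group.

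The figures assume a binary efficacy outcome, equal group sizes, the printed rates for C and D, and an unadjusted two-sided 0.05 for each contrast. A multiplicity adjustment or a continuity correction would lower the power further. How 88% was reached cannot be determined from the document.

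**What to change.** In Sample size:

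- Replace the single 80% for C, D and E with the power of each pairwise contrast at 72 and at 90 per group, and say which contrast or overall test the group size was chosen for.
- Label 88% as an assumption for a combination not previously reported, and show E v C and E v D power over a range of E, for example 75% to 88%.
- State that a non-significant E v C result does not show that adding NB-UVB gives no benefit.

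This takes a few sentences and a small table. It needs no extra patients and changes no treatment or visit. The cost is a less favourable stated power for two of the three contrasts.
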